# Evaluating the effectiveness of personal resilience and enrichment programme (PREP) for HIV prevention among female sex workers: a randomised controlled trial

**DOI:** 10.1186/1471-2458-13-683

**Published:** 2013-07-26

**Keywords:** Randomised controlled trial, Female sex workers, HIV prevention, Resilience, Protocol

## Abstract

**Background:**

Female sex workers (FSWs) are often considered as the vector, if not reservoir, of HIV and other sexually transmitted infections. Building upon the existing evidence on the role of psychological health in sexual health, the aim of this protocol is to describe a trial investigating the effectiveness of the Personal Resilience and Enrichment Programme (PREP), a resilience-promoting intervention that targets at psychological well-being i.e. self-esteem, self-efficacy and coping, to facilitate adaptation and ultimately safe sexual practices among FSWs, which could be an innovative strategy in controlling the spread of these infections.

**Methods:**

A total of 132 FSWs will be recruited and randomly assigned to either the intervention or usual care (control) groups in a multi-centred randomised controlled trial. Based on the resilience framework, this intervention is comprised of six weekly sessions focused on the awareness, expression and management of emotions, identifying roles and personal strengths, and effective problem-solving skills. Complex intervention assessment on both intervention process and effectiveness will be adopted when the primary outcome reduction of sexual risk behaviour and other psychological outcomes include their perceived stress, self-esteem, self-efficacy, coping overall resilience, and psychological distress will be measured at baseline, post-treatment and 3-month post-intervention and differences assessed by ANOVA. The relationship of resilience factors, psychological health and HIV preventive behaviours will be evaluated using structural equation modelling.

**Discussion:**

It is anticipated that this study will increase our understanding of the relationships between individual resilience attributes, positive adaptation, psychological health and sexual health practices. If successful, this programme will provide an innovative direction for HIV prevention by applying the personal resilience factors to promote both psychological well-being and safe sex for this high risk population.

**Trial Registration:**

ChiCTR-PRC-13003091

## Background

HIV infection remains a global public health challenge. In low-to-middle income countries in Eastern Europe and Asia, there was a 25% increase in new infections between 2001–09 [1]. In order to reduce transmission and the spread of infections, targeted programmes at high-risk populations are essential [2]. Among various high-risk groups, female sex workers (FSWs), who are associated with a greater number of sexual partners compounded by high mobility, have been identified to play a significant role in the transmission of HIV and other sexually transmitted infections (STIs) [3]. This is due to the fact that FSW could potentially act as a “bridge” to spread the virus to their clients and families of their clients and so forth to the general public, and to the neighbouring regions and vice versa. According to the Global Health Sector Strategy on HIV/AID 2011–15 recently published by the World Health Organisation (WHO), identifying and optimising contextually-tailored HIV prevention programmes for high risks populations was strongly recommended [4].

Current HIV prevention strategies for FSWs include harm reduction, biomedical and structural interventions operating at individual and population levels. Systematic reviews on the effectiveness of these HIV prevention programmes indicated that harm reduction programmes based on the Health Belief Model [5], Theory of Reasoned Action [6], or Theory of Planned Behaviour [7] are commonly used and mainly involve promoting condom use by increasing associated knowledge, removing barriers for access, or changing their beliefs and attitudes. In addition, interventions targeted at FSWs are effective [8,9]. Nonetheless, these programmes seldom address the issues that initially bring these women into commercial sex and the associated psychological distress. It is thus argued that since many of these interventions do not take into consideration the emotion and personal circumstances of the target population, they are unlikely to have sustainable effects [10].

Indeed, there is strong evidence of poor psychological health among FSWs associated with sex work, such as lower quality of life, higher likelihood of self-harm, anxiety and depression [11-13]. The long waiting hours for business, risks of being verbal abused, physically attacked, raped or even robbed by clients, along with the stigma attached to sex work and other related personal life circumstances [14] are together highly stressful. A number of studies have reported that FSWs with psychological distress were more likely to engage in HIV related risk behaviours such as substance abuse and inconsistent condom use [15-17]. Therefore, developing effective interventions to reduce their psychological distress and improve psychological well-being could have considerable potential in informing future directions for HIV prevention.

### Resilience as a new direction for HIV prevention

When individuals are exposed to traumatic or stressful situations, some may display psychological distress while others may have the ability to positively adapt to adversity and function competently. Such positive adjustments are referred to as *resilience*[18-20]. Based on the personal, familial, and environmental factors identified in previous studies, several prevention interventions have been proposed and demonstrated their effectiveness amongst young people; for example, the Bounce Back program [21], the Bright Ideas [22] for promoting resilience and coping skills, the Penn Resiliency Program [23] for promoting optimism and preventing depression, and the Stress Inoculation Training [24,25] for preventing anxiety amongst adolescents.

Amongst the few controlled studies investigating resilience training in adults, several have significantly improved participants’ psychological well-being and lowered distress. For example, the Well-being Therapy [26], based on Ryff’s multidimensional model of psychology well-being [27] including autonomy, personal growth, environmental mastery, purpose in life, positive relations and self-acceptance, was delivered in 4-to-8 sessions every other week and found to be effective in enhancing psychological well-being in adolescents and adults when tested alone or with cognitive-behavioural techniques [28,29]. Another resilience programme, the Transforming Lives through Resilience Education [30] which comprised four two-hour sessions, has shown to promote resilience and coping strategies through psycho-education, cognitive strategies, social skills training in college students.

Although the aforementioned studies have shown long-term improvements in psychological outcomes, there are potential difficulties in directly applying these resilience-promotion programmes to a marginalised group of women such as FSWs, who face specific but different sets of stressors and life circumstances from women who are not sex workers. With that aim in mind, our team has conducted a qualitative study on 23 FSWs in Hong Kong in 2012 [31]. FSWs interviewed in this study reported perceived and public stigma to the extent that they would not disclose their occupation and tended to reduce contact with their friends, partners or family which implied a paucity of social or family support and resources that could be drawn upon. As a result, unitising resources that lie within an individual would be a more important and acceptable approach to enhance positive adjustment in this population.

Researchers have identified a number of resilience factors which enable an individual to function competently in stressful situations. Individuals with high self-esteem were more likely to engage in health-promoting behaviours, such as using condoms or other contraceptives regularly [32] whereas people with low self-esteem and negative mood reported an increased propensity to engage in unprotected sex [33]. In addition to self-esteem, self-efficacy which refers to an individual’s belief in their ability to achieve desired goals [34], is another resilient factor that protects individuals against minor and major stresses [35,36], and promotes physical well-being. The Transactional Model of Stress and Coping [37,38] proposes that when a person faces stressful events, he or she would evaluate the situation to determine which types of coping strategies they would engage in [39]. Results from two large scale surveys in USA [40,41] investigating life stress, coping and psychological distress suggested that people who had used more coping strategies in response to stressors reported lower levels of emotional distress. This was also illustrated in our qualitative study in that FSWs who possessed personal strengths of greater self-esteem, stronger feeling of self-efficacy appeared to be associated with a reduced risk of psychological problem, lower sexual risk behaviours and better psychological well-being. Thus, the active engagement of positive psychology and resilience that strengthen and promote personal resources found within FSWs may provide a new direction for remediating stress, promoting self-esteem and thus better self-care and safe sex.

#### Research aims and objectives

The Personal Resilience and Enrichment Programme (PREP) has been developed according to resilience framework for a trial with FSWs in Hong Kong. The aim of this study is to seek a new direction for HIV prevention by investigating the effectiveness of PREP in FSWs. Through promoting FSW psychological health, it is hypothesised FSWs will take better care of their physical well-being and actively practise HIV preventive measures, and hence reduce their HIV risks. Specifically, the objectives of this study include:

1. To evaluate the effectiveness of PREP, the resilience-promoting intervention, in enhancing FSWs’ overall resilience, reducing their psychological distress, and eventually reducing HIV risk behaviours among FSWs in Hong Kong.

2. To explore the mechanism of how individual resilience factors operate to promote better psychological outcomes and decreasing HIV infection among FSWs.

This study is a randomised controlled trial to test the hypothesis that the participants in intervention group, as compared to those in the control group receiving usual care, would have an improvement in HIV preventive behaviour through the increase in overall resilience and in terms of their self-efficacy, self-esteem and coping strategies. At the same time, it is hypothesised that this cohort of FSWs’ psychological distress would be reduced upon completion of the programme and such improvements would be continued at least in the 3-month post-intervention period. The study will further explore the operation of the resilience model by specifying the association of stress perceived by FSWs, and the effects of the resilience attributes (self-esteem, self-efficacy, and coping strategies) on their level of psychological health and HIV preventive behaviours (Figure 1).

**Figure 1 F1:**
[figure not shown]
Proposed model of individual resources in predicting HIV risk behaviours.

## Methods & design

### Study design

This is a randomised controlled trial in which participants will be randomly assigned to either intervention group or usual care as the control group. Participants in the intervention condition will receive the 6-session PREP, whereas participants in the control group will receive usual care. Outcome measures of all participants will be collected at baseline, completion of intervention or 6 to 12 weeks after baseline for control group, and 3 months thereafter.

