### Intervention procedure

Participants in the intervention group will receive 6 one-hour group sessions at one-to-three week intervals. There will be 3 to 6 participants in each group. These sessions target at the three major psychological resilient factors of self-esteem, self-efficacy (e.g. praise and self-rewards will be used) and coping flexibility based on resilience framework. The programme will be conducted in a group setting so that role-plays and group modelling and interactions will be used. Such an approach, informed by Social Cognitive Theory [34], espouses that individuals can learn from the actions of another person and from the regular reinforcement a person receives. Activities in these sessions will incorporate examples of their experience in daily life and at work aimed at promoting their awareness and expression of their emotions and thoughts, management of their emotions. Since the current intervention aims to promote psychological well-being, it also draws on the approach used by previous resilience interventions, including recognising and sharing positive thoughts and emotions, identifying personal strengths and ability, introducing a variety of coping strategies, and planning using their skills and strengths to achieve goals in the future. The outline of each session is listed in Table 1.

**Table 1 T1:** Programme Outline of PREP

**Session**	**Contents**
1. Starting out	Goal-setting, encouraging awareness and expression of emotions in reaction to events
2. Empowering interpretation	Emotion management, identifying negative thoughts and generating helpful thoughts
3. Effective problem-solving	Exploring effective coping strategies, practicing problem-solving with case scenarios
4. Who am I?	Recognising their roles, giving each other affirmation
5. The unique self	Identifying successful experiences and their strengths, expressing gratitude to others
6. Preparing for the future	Exploring obstacles and using their resources to deal future challenges

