The programme will be conducted by the first author, who is a clinical psychologist supervised by the investigators based on a programme manual with objectives, outlines, activities and hand-outs. While participants must attend the first and the last sessions in order, they are able to attend the other four “stand alone” session in an order according to their schedule. Based on our previous work with FSWs, special arrangements are proposed to address the practical and psychological needs to increase participation rates: (1) FSWs will be initially contacted and subsequently followed up by the outreach staff of the NGOs, whom they have established long-term contact and trust; (2) stand-alone sessions and a more flexible time intervals are unique from usual cognitive behavioural therapy schedule in order to accommodate the mobile and erratic job nature of FSWs; (3) a relatively small group size of 3–6 persons will allow the participants to share their emotions and experiences in application of the newly acquired skills.

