### Process evaluation

The process evaluation will examine the fidelity of intervention on five different domains proposed by the National Institutes of Health Behavior Change Consortium (BCC) [57], namely design of study, training provider, treatment delivery, receipt of treatment, and enactment of treatment (see Table 2). If the programme is found to be effective, a cost-effectiveness evaluation will then be conducted.

**Table 2 T2:** Process evaluation of PREP

**Areas**	**Goals**	**Strategies**
*Design of study*	1. To ensure intervention is developed based on relevant theory.	Literature review was conducted; intervention is based on resilience framework.
	2. To ensure “dose” across is adequately described.	Participants in intervention arm will received 6 one-hour sessions and each session one-to-three week apart; field note of each session and service received by the participants will be recorded.
*Training of provider*	3. To ensure group facilitator acquires the skills and sustains over time.	Use standardized training manuals and materials for training; role playing the sessions; external quality assurance through bi-weekly meeting with investigative team throughout the study.
*Delivery of treatment*	4. To ensure intervention delivered adheres to treatment protocol and minimize differences within intervention.	Use of an intervention manual; facilitator will take field notes of the session; Helpers will rate the adherence with a checklist; have member of investigative team to observe selected sessions; record any protocol deviations.
	5. To minimise contamination between intervention and control conditions.	Advise participants not to disclose the condition they are in; conduct interviews with selected participants in control group to ensure they do not receive treatment; train the staff of NGOs the rationale of the two conditions.
*Receipt of treatment*	6. To ensure participants understand the information provided in the sessions and they are able to perform the skills learnt.	Use of active questioning to assess their understanding; record their attendance; rate their involvement in each session by group facilitator, participants and/or session helper; Use discussion role-play to ensure participants’ understand the contents.

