### Data analyses

First of all, the baseline demographics of the intervention and control groups will be compared with independent sample *t*-tests for continuous variables and *chi*-square for categorical variables to assess the compatibility of the two-trial arms at baseline to ensure both groups were similar to start with. The change of scores on sexual health risks and psychological outcome measures (self-esteem, self-efficacy, coping, resilience and GHQ) over time between two groups will be analysed using analysis of variance with intention-to-treat analysis. Bivariate correlation analyses will be performed to examine the relationship between psychological variables and behavioural outcomes. Linear regressions will also be used to examine the associations and the effects of resilience, self-esteem, self-efficacy, coping on psychological health outcomes and HIV preventive behaviours. The statistical analyses will use SPSS 20.0 and *p*-values of 0.05 or less will be considered statistically significant.

The second objective of the current study is to explore the mechanism of how individual resilience factors influence the psychological outcomes and HIV preventive behaviours in FSWs (as proposed in Figure 1). Structural equation modelling (SEM) identifies connection strengths that best predict the observed structure of the data with respect to the specified model. Thus, SEM will be performed to evaluate the model fit of the proposed model that links psychological resources with harm-reduction behaviours as measured by condom use.

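### The two arms are assessed on different clocks: programme completion for PREP, weeks since baseline for controls; the windows overlap but do not match, and PREP non-completers have no stated date

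*Protocol article*

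**What the plan says.** **Assessment times.** Study design sets a baseline assessment for everyone, then assessments at "completion of intervention or 6 to 12 weeks after baseline for control group, and 3 months thereafter". No limit in weeks is given for the PREP arm.

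**Programme length.** Intervention procedure says: "Participants in the intervention group will receive 6 one-hour group sessions at one-to-three week intervals". The process-evaluation table repeats it: "Participants in intervention arm will received 6 one-hour sessions and each session one-to-three week apart". The abstract says something else: "this intervention is comprised of six weekly sessions".

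**Flexibility.** The first and last sessions keep their place, but for the rest "they are able to attend the other four “stand alone” session in an order according to their schedule". The same section explains that flexible intervals are deliberate, because the women's work is mobile and irregular. On group size: "There will be 3 to 6 participants in each group".

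**Analysis.** Changes over time between groups "will be analysed using analysis of variance with intention-to-treat analysis". The primary outcome is self-reported condom use with clients over the month before the assessment and at the last encounter, so the period it covers moves with the assessment date.

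**The concern.** In a two-arm comparison of change over time, the time since randomisation at each assessment should have the same distribution in both arms. Here it is set by attendance in one arm and by a range of weeks in the other. Since the primary outcome looks back one month, the month it describes can fall at a different distance from baseline in each arm.

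The second issue is who has a date at all. Every control has one, because hers does not depend on what she does. A PREP woman's date depends on finishing the programme, so under the stated rule a woman who stops has none. An intention-to-treat analysis needs outcomes for these women at a time comparable with the controls. If sites improvise the date or skip the visit, the analysis cannot recover what was lost. The Limitations section discusses drop-out in the usual-care arm only.

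**Working it through.** **Inputs.** Six sessions, one to three weeks apart (Intervention procedure; process-evaluation table). Control window 6 to 12 weeks after baseline, final visit three months after the second assessment (Study design). Weekly sessions (abstract).

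**1. Can the control window be reproduced from the programme?** Six sessions have 6 − 1 = 5 gaps.

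| Spacing | First to last session |
|---|---|
| 1 week | 5 × 1 = 5 weeks |
| 2 weeks | 5 × 2 = 10 weeks |
| 3 weeks | 5 × 3 = 15 weeks |

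One-to-three week spacing gives 5 to 15 weeks. Weekly spacing gives 5 weeks. Neither gives 6 to 12. That range equals 6 × 1 to 6 × 2, which corresponds to no spacing stated in the article.

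**2. Second assessment, taking session 1 at baseline.**

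- Slow end: 15 − 12 = 3 weeks after the last control date.
- Fast end: 6 − 5 = 1 week before the earliest control date.
- A PREP woman falls inside the control window if her average gap lies between 6/5 = 1.2 and 12/5 = 2.4 weeks. The permitted range is 1 to 3.

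**3. Wait between baseline and session 1.** None is stated. Assembling a group of three to six women could cause one, so I treat it as an assumption of 0 to 4 weeks. The upper end then becomes 15 to 19 weeks and the lower end 5 to 9. Any wait pushes the PREP arm later; a wait of one week or more removes the early overhang and lengthens the late one.

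**4. Three-month visit**, taking three months as 13 weeks and no initial wait.

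| Arm | Second assessment | Final assessment |
|---|---|---|
| PREP | 5 to 15 weeks | 5 + 13 = 18 to 15 + 13 = 28 weeks |
| Control | 6 to 12 weeks | 6 + 13 = 19 to 12 + 13 = 25 weeks |

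The same 1-week and 3-week overhangs reappear.

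**5. Non-completers.** Setting Study design beside Data analyses: the first gives completion as the only trigger in the PREP arm, and the second calls for intention-to-treat. The article states no fallback date that would connect the two.

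**The case against.** The strongest defence is that the windows largely agree. The control window is itself six weeks wide and lies wholly inside the 5 to 15 week range; the midpoints are 9 weeks (control) and 10 weeks (PREP). That stands. It means the mismatch concerns women at the fast and slow ends, and without a distribution of completion times nobody can say how many there will be.

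Several stronger readings are tempting, and the document does not support them.

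- *A nine-week gap.* 15 − 6 = 9 pairs the slowest PREP woman with the earliest control. The opposite pairing, 12 − 5 = 7 weeks, runs the other way. Neither describes the typical difference.
- *Non-completers will go unassessed, leaving only motivated women in the PREP arm.* Study design says measures are collected from all participants, and the analysis is by intention to treat. What is missing is a stated date, not a commitment to assess. The full protocol may hold a fallback.
- *The bias favours PREP.* Nothing in the article shows a drift in condom use over a few weeks, or its sign. For fast attenders the one-month recall overlaps the programme, but that is inherent in an end-of-programme measure and, if anything, might dilute an effect.

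A further defence is that the research hypothesis concerns improvement on completing the programme, so anchoring to completion is sensible for a flexible schedule. That explains why a post-programme measure is wanted. It does not explain why controls should be on a separate clock, since control dates can be tied to the PREP dates without losing that measure.

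**Conclusion.** The point holds in a limited form. The article states a timing rule that differs by arm, and the control window does not follow from the trial's own session spacing. At the permitted extremes the PREP assessment falls up to 3 weeks after the last control date or 1 week before the earliest, and the final visit inherits this. These figures take session 1 at baseline; an unstated wait would shift the PREP arm later. The stated rule also leaves PREP non-completers without a date, which sits badly with intention-to-treat.

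A reader might infer that time since baseline is wholly confounded with arm, or that the result is biased towards PREP. The ranges overlap too much for the first, and the document has no data for the second: the size and direction of any bias are undetermined. The case for change is that this is an avoidable difference between the arms that is cheap to remove before data collection and hard to repair afterwards. The sample size is not affected.

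**What to change.** 1. Set each control's second assessment to match the assessment date of PREP women randomised at about the same time. Alternatively, use one common window from baseline in both arms that covers the permitted programme length.
2. Time the three-month visit from that same date in both arms.
3. State that every randomised woman is assessed at those dates regardless of attendance, so that a PREP woman who stops is seen when her concurrently randomised peers are.
4. Reconcile the session spacing in the abstract with that in Intervention procedure and the process-evaluation table, and both with the 6 to 12 week window in Study design.

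**Cost.** Wording changes and somewhat more scheduling work, with no change in sample size. Matched dates keep the measure close to the end of the programme, though some women will be seen a few weeks after their last session. The common window costs more on this count: if it were placed at 15 weeks, a weekly attender would be assessed about 15 − 5 = 10 weeks after her last session, close to the planned three-month follow-up. Matching is therefore the better first choice.
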